## SUMMARY

Following the rapid development of significant drug resistance of *Plasmodium falciparum* (Pf) to chloroquine and then sulfadoxine-pyrimethamine, artemether-lumefantrine (Coartem or AL) was adopted as first line therapy in Ethiopia in 2004. According to the current national malaria diagnosis and treatment guidelines updated in 2012 [1], first-line treatment for uncomplicated *P. falciparum* infection is AL. First-line treatment for *Plasmodium vivax* (Pv) is chloroquine (CQ) alone in malarious areas and with primaquine in non-malarious areas at health center and hospital level. WHO recommends treatment of Pv with CQ or an artemisinin-based combination therapy (ACT) in combination with primaquine [2]. For all clinical infection without laboratory confirmation, AL is the first-line treatment since AL is effective against both Pf and Pv. Thus, in Ethiopia, where treatment for malaria without laboratory confirmation occurs frequently, Pv is often treated with AL as the standard of care. Similarly, the recommended drug for mixed infection with Pf and Pv is AL. Now with wide-spread use of AL and CQ and with evidence that malaria laboratory testing is occurring in about half of those suspected with clinical evidence of malaria infection, we propose to conduct an antimalarial efficacy study to monitor the effectiveness of these therapies in Ethiopia and to determine how efficacious these drugs remain for Pv. In addition, with high rates of relapse with *P. vivax* infection, the efficacy and safety of co-administering primaquine will be assessed. This information will inform future policy changes with respect to appropriate antimalarial strategies.

In this proposal, patients aged above 1 year with symptomatic malaria presenting to health centers will be enrolled for treatment with AL, AL+PQ, CQ, or CQ+PQ, for vivax infection. Phase 1 of the study will monitor the clinical, parasitological, and hematological parameters for *P. vivax* infection over a 42-day follow-up period, which will be used to evaluate drug efficacy. Phase 2 will continue monthly follow-up of these patients for one year to assess frequency of recurring vivax infections. Results from this research study will be used to assist Ethiopia in assessing their current national malaria drug policies.

## INTRODUCTION

Malaria in Ethiopia is highly unstable, with potential for epidemics. In Ethiopia, malaria transmission is largely determined by climate and altitude. Most of the transmission occurs between September and December, after the main rainy season from June to August. Malaria is the leading communicable disease in Ethiopia. In 2009–2010, malaria was the most common cause of outpatient visits and admissions, accounting for 14% of all visits and 9% of admissions [3]. About 75% of the country is malarious (defined as areas <2000 m), with about 68% (i.e. 52 million) of the country's total population living in areas at risk of malaria.

*P. falciparum* (Pf) and *P. vivax* (Pv) are the two dominant parasite species with relative frequencies of 60% and 40%, respectively, although this relative proportion varies both temporally and spatially, with published ranges of 22–89% for *P. falciparum* and 11–67% for *P. vivax* [4–6]. Chloroquine (CQ) resistant Pf was first reported from Africa in 1978 [7] and became a major public health threat to Ethiopia in the 1990s. With reports of wide-spread Pf resistance to CQ [8] and sulphadoxine-pyrimethamine (SP) [9, 10], the Federal Ministry of Health (FMOH) adopted artemether-lumefantrine (AL) for first-line treatment of uncomplicated *P. falciparum* malaria in 2004 [11]. Although CQ remained the first-line treatment for *P. vivax* malaria in Ethiopia, AL is used widely for all cases of clinical malaria where diagnostics to determine the specific malaria species are not available and for mixed infections.

Following the first report of CQ resistant *P. vivax* in 1989 from Papua New Guinea [12], decreased CQ susceptibility of <50% [13] has been reported from Indonesia [14–17] and Papua New Guinea [18]. Decreased susceptibilities of 50–90% have been reported from Burma/Myanmar [19], Vietnam [20, 21], Turkey [22, 23], Colombia [24], and Brazil [25]. Overall, CQ resistant *P. vivax* has remained rare in Africa. In 1996, Ethiopia published its first report of CQ resistance, with 2% (5/255) of study patients failing at day 7 [26]. Subsequent reports from Ethiopia documented presence of CQ-resistant *P. vivax*, but at levels not exceeding 5% [27–29]. A recent study from SNNPR noted 13% treatment failure but they did not measure CQ levels [30].

*P. vivax* unlike *P. falciparum* has a dormant stage [hypnozoites] that can persist in the liver and cause relapses by invading the bloodstream weeks, or even years later. Both CQ and AL treat only the *P. vivax* blood stage parasites, resulting in a short-term clinical cure, but these medicines do not eliminate the liver stage infection, leaving the patient at risk of later malaria illness relapses. In a study conducted in Ethiopia in 2009, CQ and AL treatments both caused clinical cures of *P. vivax* malaria lasting up to three weeks in all patients; however, unacceptably high rates of recurrent *P. vivax* parasitemia were noted at 42 days of follow-up, with 41.6% (47/113) in the AL arm and 34% (34/107) in the CQ arm (unpublished data). Many of these recurrent malaria parasitemias were likely caused by relapses of dormant infections, although some probably were from new *P. vivax* re-infections. *P. vivax* infection is ideally treated with either CQ or AL resulting in a clinical cure, then with primaquine (PQ) resulting in a radical cure by eliminating the dormant liver hypnozoite forms. Primaquine radical cure is the standard of care in malaria-free areas such as the United States to prevent relapses and primaquine is the recommended WHO policy for adequate Pv treatment [2].

One study assessing the efficacy of CQ vs. AL both given with primaquine noted cure rates of 97.4% for AL vs. 100% for CQ at day 28 in Thailand [31]. In Ethiopia, the addition of primaquine to CQ decreased the cumulative incidence of therapeutic failure at day 28 by a life-table analysis method from 5.76% to 0.75% and the cumulative risk of relapse at day 157 by a life-table method from 61.8% to 26.3% [32].

Primaquine was previously widely used in Ethiopia according to national malaria treatment guidelines until the late 1990's. However, due to G6PD-related safety concerns that were mostly reported in other countries, primaquine use is now limited to Ethiopian health facilities with good laboratory capacity in non-malarious areas typically located above 2000m altitude. There is currently limited G6PD testing capacity in Ethiopia. The Ethiopian national malaria program is very interested in gathering credible evidence to support the scale up and safe deployment of primaquine for *P. vivax* treatment as the country moves towards malaria elimination.

In addition to assessing the efficacy of AL or CQ alone for *P. vivax* treatment, we propose to improve our understanding of the safety and the efficacy of primaquine use in G6PD non deficient patients in combination with these medications through a randomised, trial comparing the current practice of not using primaquine for most *P. vivax* cases with the WHO recommended standard therapy for *P. vivax* malaria (PQ 0.25mg/kg daily for 14 days).

## OBJECTIVES

To assess the therapeutic efficacy of AL compared to AL+PQ and CQ compared to CQ+PQ for *P. vivax* infection and to determine the number of recurrent vivax episodes in patients receiving PQ compared to those who don't receive PQ.

### Specific Objectives

#### Phase 1:

- 1) **Efficacy:** To measure the clinical and parasitological efficacy of AL, CQ, AL+PQ, or CQ+PQ for *P. vivax* infection during a 42-day follow-up period. (See Annex I for WHO definitions of *P. vivax* treatment failures)
- 2) **Safety:** To compare changes in hemoglobin concentration following vivax infection in patients receiving PQ versus patients who don't receive PQ.

#### Phase2:

- 1) **Efficacy:** To measure the clinical and parasitological efficacy of AL vs. AL+PQ, or CQ vs. CQ+PQ among patients  $\geq 12$  months of age suffering from uncomplicated vivax malaria by determining the number of recurrent vivax episodes (symptomatic as well asymptomatic) in patients receiving PQ versus patients who don't receive PQ during a 12 month follow up period.

## STUDY DESIGN

This trial is a randomised, open label evaluation of clinical and parasitological responses to directly observed treatment for uncomplicated *P. vivax* malaria. Patients with uncomplicated *P. vivax* malaria infection who meet the study inclusion criteria will be enrolled, randomised, and treated on site with either AL or CQ with or without PQ, and monitored for 12 months. The drug administration will be directly observed. The follow-up will consist of a fixed schedule of check-up visits and corresponding clinical and laboratory examinations. On the basis of the results of these assessments, the number of adverse events and number of relapses will be compared between the study arms.

### Study Sites

Evaluation sites in Oromia Regional State will be selected based on availability of adequate numbers of cases of symptomatic, uncomplicated *P. vivax* malaria infections, and willingness of the selected health care facility staff to participate in the study and to support the work with laboratory space. All sites will be public health centers operated by the Oromia Regional Health Bureau. We

have preliminary selected Bishoftu Malaria Control Center and Bulbula Health Center based on epidemiologic data, but we will continue to follow the malaria situation at these sites to determine the need for replacement sites from other districts and health facilities in Oromia Regional State in Ethiopia in order to obtain sufficient patient numbers for recruitment.

## **Drugs**

All drugs will be GMP-certified and obtained from WHO.

### **Known efficacy and adverse effects of treatment drugs**

- **Artemether - lumefantrine (Coartem or AL):** AL is currently the first line anti-malarial recommended by Ethiopian Ministry of Health for the treatment of uncomplicated falciparum infection, mixed Pf and *P. vivax* infections, and treatment of clinical malaria cases without laboratory confirmation which comprises of non-malaria cases, falciparum cases, and vivax cases. It is also an alternative medication for *P. vivax* infection when CQ is unavailable in Ethiopia. Adverse events are generally mild, most commonly gastrointestinal (GI) (vomiting and diarrhea) and hematologic (anemia and eosinophilia) [33]. Its safety was demonstrated in studies from Ethiopia and Uganda and in many other countries [34, 35].
- **Chloroquine (CQ):** Chloroquine, a 4-aminoquinoline, was recognized as an effective and safe antimalarial in 1946, and was the most widely used drug against malaria until significant resistance to chloroquine rendered it ineffective against *P. falciparum* by 1999. CQ is currently recommended by Ethiopian Ministry of Health for the treatment of *P. vivax* infection. Resistance to CQ has been described mostly in Southeast Asia in *P. vivax*, but available evidence shows relatively low levels of resistance in Ethiopia. Side effects include dizziness, skeletal muscle weakness, mild GI disturbances (nausea, vomiting, abdominal discomfort, and diarrhea), and pruritus [36].
- **Primaquine (PQ):** Primaquine is an 8-aminoquinoline and is effective against intrahepatic forms of all types of malaria parasite. It is used to provide radical cure of *P. vivax* and *P. ovale* malaria, in combination with a blood schizontocide such as CQ or AL for the erythrocytic parasites. The most important adverse effects are hemolytic anemia in patients with glucose-6-phosphate--dehydrogenase (G6PD) deficiency. In patients with the most common African variant of G6PD deficiency, the standard course of primaquine generally produces a benign self-limiting anemia. Therapeutic doses may also cause abdominal pain if administered on an empty stomach. Larger doses can cause nausea and vomiting. Methemoglobinaemia may occur. Other uncommon effects include mild anemia and leukocytosis. The severity of hemolytic anemia is related to primaquine dosing and the variant of the G6PD enzyme. Fortunately, primaquine is eliminated rapidly and so hemolysis is self-limiting provided no further drug is taken.

**Drug Dosing and Regimens:** All patients will be weighed to determine the accurate weight-based dose for both drugs.

- **Artemether-lumefantrine (Coartem; Novartis)** administered twice daily for three days as tablets containing 20 mg of artemether plus 120 mg of lumefantrine in a fixed dose combination at a dosage [37].

| Weight (kg) | Age      | Day 1   |         | Day 2   |         | Day 3   |         |
|-------------|----------|---------|---------|---------|---------|---------|---------|
|             |          | Morning | Evening | Morning | Evening | Morning | Evening |
| 5–14        | 3mo–2yrs | 1       | 1       | 1       | 1       | 1       | 1       |
| 15–24       | 3–7 yrs  | 2       | 2       | 2       | 2       | 2       | 2       |
| 25–34       | 8–10 yrs | 3       | 3       | 3       | 3       | 3       | 3       |
| > 35        | 10+ yrs  | 4       | 4       | 4       | 4       | 4       | 4       |

- **Chloroquine:** Total of 25mg base per kg over 3 days (10 mg base/kg on Days 1 and 2, and 5 mg base/kg on Day 3) [37]. 500 mg tablets and 10mg/ml syrup formulations.

| Weight (kg) | Age       | Day 1                       | Day 2                       | Day 3                      |
|-------------|-----------|-----------------------------|-----------------------------|----------------------------|
| 5–6         | <4 mo     | ¼ tablet
(5 ml syrup)    | ¼ tablet
(5 ml syrup)    | ⅛ tablet
(2.5 ml syrup) |
| 7–10        | 4–11 mo   | ¼ tablet
(7.5 ml syrup)  | ¼ tablet
(7.5 ml syrup)  | ¼ tablet
(5 ml syrup)   |
| 11–14       | 1–2 yrs   | ½ tablet
(12.5 ml syrup) | ½ tablet
(12.5 ml syrup) | ¼ tablet
(7.5 ml syrup) |
| 15–18       | 3–4 yrs   | ½ tablet
(15 ml syrup)   | ½ tablet
(15 ml syrup)   | ½ tablet
(15 ml syrup)  |
| 19–24       | 5–7 yrs   | ¾ tablet
(20 ml syrup)   | ¾ tablet
(20 ml syrup)   | ½ tablet
(15 ml syrup)  |
| 25–35       | 8–10 yrs  | 1¼ tablet                   | 1¼ tablet                   | ½ tablet                   |
| 36–50       | 11–13 yrs | 1½ tablet                   | 1½ tablet                   | 1 tablet                   |
| > 50        | 14+ yrs   | 2 tablet                    | 2 tablet                    | 1 tablet                   |

- **Primaquine:** 0.25 mg/kg daily for 14 days will be administered on days 2-16 to those with a confirmed normal G6PD test by NADPH fluorescent spot test, which is the most commonly used test and is currently recommended by the International Committee for Standardization in Hematology.

| Body weight (kg)   | mg                 | Number of 15mg tablets |
|--------------------|--------------------|------------------------|
|                    | based on 0.25mg/kg | PER DAY FOR 14 DAYS    |
| 5-14               | 1.25 to 3.5        | ¼                      |
| 15-24              | 3.75 to 6          | ¼                      |
| 25-34              | 6.25 to 8.5        | ½                      |
| 35 -60
And more | 8.75 to 15         | 1                      |

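### The chloroquine table contradicts the daily split stated above it, pairs tablets with syrup inconsistently, and rests on a tablet strength not labelled salt or base

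*Protocol*

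**What the plan says.** Under Drugs, Drug Dosing and Regimens, the protocol gives the chloroquine regimen in three forms.

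- A rule in mg base per kg: "Total of 25mg base per kg over 3 days", divided as "10 mg base/kg on Days 1 and 2, and 5 mg base/kg on Day 3".
- A formulation line: "500 mg tablets and 10mg/ml syrup formulations". Neither strength is labelled as salt or base.
- A table of eight weight bands with tablet fractions for each day. The five bands up to 24 kg also carry syrup volumes.

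The 7–10 kg row reads "¼ tablet (7.5 ml syrup) | ¼ tablet (7.5 ml syrup) | ¼ tablet (5 ml syrup"). The 15–18 kg row reads "½ tablet (15 ml syrup) | ½ tablet (15 ml syrup) | ½ tablet (15 ml syrup").

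Under Intervention or treatment, staff supervise every chloroquine dose. Under Efficacy end points, CQ against CQ+PQ is one of the two primary comparisons.

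**The concern.** The text fixes both a total and a split, and the table is what staff would follow when they hand out doses. A row with the same amount on all three days cannot deliver 10, 10 and 5 mg/kg at any strength. Where the tablet and the syrup in one cell are different amounts, a child's dose depends on the formulation used as well as on weight. Where the tablet strength has no salt or base label, the tablet column cannot be checked against a rule written in base.

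At stake is whether the regimen described is the regimen given, mainly in the paediatric bands. Chloroquine levels are measured on the day of recurrence (Drug level testing), and those results are read against a regimen that the protocol does not define consistently.

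**Working it through.** **Inputs.** All come from Drugs, Drug Dosing and Regimens: the 10/10/5 rule, the 25 mg base/kg total, syrup at 10 mg/ml, and the table entries. The syrup strength is read as base, which is an assumption because the line does not say so.

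**Step 1: reproduce the stated figures from the syrup.** Dose = ml × 10 ÷ weight, at the upper and lower limit of each band.

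| Band (kg) | Syrup, ml (Days 1, 2, 3) | Day 1 mg/kg | Day 3 mg/kg | Total mg/kg |
|---|---|---|---|---|
| 5–6 | 5, 5, 2.5 | 8.3–10.0 | 4.2–5.0 | 20.8–25.0 |
| 7–10 | 7.5, 7.5, 5 | 7.5–10.7 | 5.0–7.1 | 20.0–28.6 |
| 11–14 | 12.5, 12.5, 7.5 | 8.9–11.4 | 5.4–6.8 | 23.2–29.5 |
| 15–18 | 15, 15, 15 | 8.3–10.0 | 8.3–10.0 | 25.0–30.0 |
| 19–24 | 20, 20, 15 | 8.3–10.5 | 6.25–7.9 | 22.9–28.9 |

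Day 1 includes 10 mg/kg and the total includes 25 mg/kg in all five rows, so reading the syrup as base is reasonable. Day 3 is where the table departs. In the 15–18 kg row it is 150 ÷ 18 = 8.3 to 150 ÷ 15 = 10.0 mg/kg against 5, an excess of 67% to 100% for that day. The same row's total is 450 ÷ 18 = 25.0 to 450 ÷ 15 = 30.0 mg/kg, 0% to 20% above 25.

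**Step 2: check the split without any strength.** Day 3 ÷ Day 1 should be 0.5.

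| Band (kg) | Tablets | Syrup |
|---|---|---|
| 5–6 | 0.50 | 0.50 |
| 7–10 | 1.00 | 0.67 |
| 11–14 | 0.50 | 0.60 |
| 15–18 | 1.00 | 1.00 |
| 19–24 | 0.67 | 0.75 |
| 25–35 | 0.40 | none |
| 36–50 | 0.67 | none |
| >50 | 0.50 | none |

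Five of eight tablet rows and four of five syrup rows depart from 0.5. Ratios between 0.4 and 0.75 may be rounding. The 15–18 kg row is not plausibly rounding: both columns are flat, and ¼ tablet and 7.5 ml are used elsewhere in the table.

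**Step 3: compare tablet with syrup.** Implied tablet strength = ml × 10 ÷ tablet fraction.

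| Band (kg) | Days 1–2 | Day 3 |
|---|---|---|
| 5–6 | 50 ÷ 0.25 = 200 mg | 25 ÷ 0.125 = 200 mg |
| 7–10 | 75 ÷ 0.25 = 300 mg | 50 ÷ 0.25 = 200 mg |
| 11–14 | 125 ÷ 0.5 = 250 mg | 75 ÷ 0.25 = 300 mg |
| 15–18 | 150 ÷ 0.5 = 300 mg | 150 ÷ 0.5 = 300 mg |
| 19–24 | 200 ÷ 0.75 = 267 mg | 150 ÷ 0.5 = 300 mg |

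The range is 200 to 300 mg, it changes within three of the five rows, and it never reaches 500. The contradiction needs no strength to be assumed: ¼ tablet is paired with both 5 ml and 7.5 ml, and ½ tablet with both 12.5 ml and 15 ml.

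**Step 4: how much could be rounding?** Assume 300 mg base per tablet, a figure the protocol does not state. Then 7 of the 15 paired cells match exactly: 7–10 kg Days 1–2, 11–14 kg Day 3, 15–18 kg all days, and 19–24 kg Day 3. Seven of the other eight are the syrup dose taken to the nearest quarter tablet (75 mg): 50 to 75, 125 to 150 and 200 to 225 mg. The eighth is the 5–6 kg Day 3 cell, "⅛ tablet (2.5 ml syrup"), where 37.5 mg stands against 25 mg. On this assumption the flat 7–10 kg tablets could also come from quarter-tablet rounding (50 mg to 75 mg on Day 3). The table nevertheless uses an eighth of a tablet in the row above, and it states no rounding rule.

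**The case against.** The strongest reply is that this is a banded table that gets the total about right. Syrup totals include 25 mg/kg in every row. At an assumed 300 mg base per tablet, 5 of 8 bands also include it, and the >50 kg row gives 1500 ÷ 60 = 25 mg/kg at 60 kg. Bands and quarter tablets always produce some spread. CQ and CQ+PQ use the same table, so the contrast between them is not biased, and chloroquine levels are measured rather than inferred from the nominal dose. All of this stands. It limits the consequences but does not remove the contradiction over the daily split or between the paired entries.

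Three stronger readings are tempting, and the protocol does not support them.

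- A reader might infer that the tablet strength fits no row. For the dose in mg/kg, that needs 500 mg to mean base, which the text does not say. What can be shown is that the label is missing and that no syrup pairing implies 500 mg.
- A reader might infer overdosing on the scale of 37.5–62.5 mg/kg in the closed bands. Those totals arise only if the supplied tablet holds 500 mg base. The table gives tablet counts, so misreading the label would not change what is handed out from it.
- A reader might infer that chloroquine patients in general would not receive the stated regimen. The 5–6, 11–14 and >50 kg tablet rows keep the 2:2:1 split, so the clear departures are confined to particular rows.

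The two lightest rows carry age labels below the entry age of more than 1 year. Dosing is by weight and entry starts at 5.0 kg, so those rows can still apply. The 15–18 kg row, labelled 3–4 years, lies well inside the eligible population.

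**Conclusion.** The point holds as an internal contradiction in the chloroquine dosing section.

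- The 15–18 kg row contradicts the stated split in both formulations, whatever the tablet strength. The Day 3 size of 8.3–10.0 against 5 mg/kg assumes that the syrup is 10 mg base per ml. The total in that row is 0% to 20% above 25 mg/kg.
- The 7–10 kg tablets are flat while their paired syrup falls by a third. Quarter-tablet rounding could produce this, but no such rule is stated.
- No single tablet strength fits the pairs (implied 200 to 300 mg). Part of the mismatch may be rounding.
- The 500 mg strength has no salt or base label in a regimen written in base.

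The matter should be put right because staff would dose from this table. It does not threaten the CQ against CQ+PQ comparison, the sample size or the type I error.

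**What to change.** Before the table is used, the sponsor should:

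1. reconcile the stated daily split, the weight-band table and the formulation line, starting with the 15–18 and 7–10 kg rows;
2. give the tablet and syrup strengths in mg base;
3. either align the paired tablet and syrup entries or state the rounding rule that explains why they differ. Exact equality in every cell should not be demanded: at 300 mg base (assumed), syrup doses of 50, 125 and 200 mg cannot be made from quarter or eighth tablets.

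Which dose is right is for the sponsor to decide. The cost is a corrected table and one clarified line in an amendment, with no effect on sample size or visits.

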## **Intervention or treatment**

**Antimalarial Therapy-** All patients will be randomized to receive AL or CQ. Once G6PD results are available, those testing normal will be randomized to PQ or no PQ.. In Ethiopia G6PD deficiency is very rare (0.5-2.9%) [38]. All doses of CQ, PQ, and morning AL will be given under supervision by the staff. The evening dose of AL will be given to the patients to take at home. Children less than 5 years of age will be given an extra evening dose in case of vomiting. Patients will be observed for 60 minutes after treatment for adverse reactions or vomiting. Those patients vomiting their medication within the first 30 minutes will receive a repeat full dose, those vomiting from 30-60 minutes will receive half dose. This is standard practice for anti-malarial treatment.

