**SCREENING AND ENROLLMENT PROCEDURES****Screening Procedures for Enrollment**

Screening for eligible patients at the two study sites will be done in the following fashion:

1. All patients presenting to the evaluation sites will be registered. At malaria treatment centers all patients will get a blood smear, whereas at health centers all patients presenting with fever will then get a blood smear. Patients with microscopy confirmed diagnosis of Pv malaria illness, age greater than 1 year, and living within 20 km of the health center will be screened for eligibility for enrollment. Those patients who for any reason are not enrolled into this study according to the screening and enrollment process will be treated promptly according to the current National Malaria Diagnosis and Treatment Guidelines [1].
2. If the patient meets the screening criteria and the patient or the parent or guardian asked for permission consents to enrollment, they will be assigned a consecutive, unique number that will become the patient's study number and will be used to identify all forms and blood samples from that patient. Enrollment will be conducted by a staff member not involved in the clinical assessment of the participant to ensure that consent is freely given.

3. A screening form containing demographic, clinical, and laboratory information will be started on each smear positive patient, thus allowing for appropriate tracking of each patient through the screening procedure.
4. The patient's body weight will be measured, using a hanging scale for weighing young children, or a floor scale for large children/ adults and recorded on the demographic form.

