### **Laboratory Evaluations:**

2. Urine pregnancy test will be conducted on all women aged 13-49 and anyone testing positive will be excluded.
3. Those enrolled will have a second finger prick performed to assess for the following:
  - Thin smear will be used to verify parasite species and thick smear to conduct a formal parasite count. Two qualified microscopists will read all the slides independently. Blood smears with discordant results (differences between the two microscopists in species diagnosis, in parasite density of > 50% or in the presence of parasites) will be re-examined by a third, independent microscopist, and parasite density will be calculated by averaging the two closest counts.
  - Hemoglobin measurement (HemoCue™ Hb 301HemoCue, Angelholm, Sweden) will be carried out and those with hemoglobin <8g/dL will be excluded.
  - Filter paper will be obtained for the purpose of genotyping to differentiate identical vs. different genotypes, potential molecular testing for resistance markers, and gametocyte testing. G6PD testing using the NADPH fluorescent spot test will be conducted at the end of each day. The NADPH fluorescent spot test is a qualitative test and those determined to be G6PD deficient will not be given primaquine.
4. Patients testing smear positive for Pv will receive AL, at one site and CQ at the other site. After G6PD testing results are available, the patients not found to be G6PD deficient will be randomized to either AL alone or AL+PQ at one study site and CQ alone or CQ+PQ at the other site. Those found to be G6PD deficient will remain in either the AL or CQ alone arms. The study will not be blinded, although microscopists reading blood films will not be aware of which arm a participant is from.
5. On day 0, each patient will receive the morning dose of treatment (AL or CQ) medication under direct observation and will be monitored for vomiting for 60 minutes. The patient or parent will be given the evening dose (for AL only) to administer at home. Each patient will return on days 1 and 2 (and up to 14 days for those in the PQ arms) for subsequent doses. Those in the primaquine arms will return on every second day on days 2-16 for directly observed therapy. Clinical reassessments will be made on days 1- 3, 7, 14, 21, 28, 35, 42, and then monthly (see Annex V and VI for a table of scheduled procedures).

Participants will be given 35 Ethiopian Birr for each visit to cover their travel expenses (this is

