#### Enrollment

Treatment, first dose with either AL or CQ  
Hemoglobin, filter paper for PCR  
Pregnancy testing, if female age 13-49 years

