### **Day 1:**

---

Clinical assessment — referral in case of severe malaria/danger signs  
Measurement of axillary temperature  
Parasitological assessment  
G6PD testing and randomization if G6PD normal  
Treatment, second dose or alternative treatment in case of early treatment failure

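### The protocol gives two incompatible rules for allocating AL or CQ; under the site-based rule, any AL versus CQ comparison is non-randomised and cannot be separated from site

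*Protocol*

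**What the plan says.** The two allocation rules are:

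- Intervention or treatment, Antimalarial Therapy: "All patients will be randomized to receive AL or CQ". Patients with a normal G6PD result are then randomised to PQ or no PQ. This is a two-step randomisation giving four arms.
- Laboratory Evaluations, item 4: "Patients testing smear positive for Pv will receive AL, at one site and CQ at the other site". Once G6PD results are known, patients who are not deficient are "randomized to either AL alone or AL+PQ at one study site and CQ alone or CQ+PQ at the other site". Here the blood-stage drug is set by place of enrolment and only PQ is randomised.

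Other places that bear on the point:

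- Screening Procedures for Enrollment gives the number of sites: "Screening for eligible patients at the two study sites will be done in the following fashion".
- Study Design labels the whole study: "This trial is a randomised, open label evaluation of clinical and parasitological responses to directly observed treatment". It adds that the "number of adverse events and number of relapses will be compared between the study arms".
- Annex VI, Day 0, Enrollment, lists "Treatment, first dose with either AL or CQ" and no randomisation. Day 1 lists "G6PD testing and randomization if G6PD normal".
- The Objectives, the Phase 2 objective and the Efficacy end points all set AL against AL+PQ and CQ against CQ+PQ.
- The Phase 1 safety objective and the Safety end points compare haemoglobin between PQ and no PQ. For adverse events, the Safety end points refer to treatment arms in general.

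**The concern.** The two rules describe different trials. Under the first, AL versus CQ is a randomised contrast. Under the second, the study is two single-site PQ trials side by side, and AL versus CQ is a comparison of two health facilities. Site staff need to know which applies before the first patient is enrolled, because the randomisation lists and the drug stock differ.

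What is at stake is the reading of any cross-drug result. The Summary says the results will help Ethiopia assess its malaria drug policies, and both AL and CQ are in use there. Someone who reads only the Intervention or treatment section would take an AL–CQ difference in recurrences or adverse events as randomised evidence. Under the site-based rule, that difference would also carry everything else that differs between the sites, such as reinfection pressure, case mix and staff.

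**Working it through.** **Step 1. Compare the rules.** There are two sites. Under the Intervention or treatment rule, each site would enrol patients on both drugs. Under item 4, one site has only AL and the other only CQ. In a model with a drug term and a site term, the two columns are then identical, so their effects cannot be estimated separately and no adjustment recovers them. The Study Sites section allows replacement sites but does not say which drug a replacement would use.

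**Step 2. See which rule the rest of the protocol supports.** Annex VI has one randomisation, on day 1 after the G6PD test and after the first AL or CQ dose on day 0. A randomisation to AL or CQ would have to come before that dose, and none is listed. This fits item 4. The Study Design wording about randomising and treating patients on site fits either rule.

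**Step 3. Ask whether the sites could differ.** The preliminary sites are a malaria control center and a health center. Screening Procedures smears all patients at malaria treatment centers but only febrile patients at health centers. If the control center follows the former practice, the routes into the study differ. The enrolment criterion of fever or recent history of fever limits this difference but need not remove it. The Introduction adds that transmission depends on climate and altitude.

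**Step 4. Check the primary contrasts and sample size.** The inputs are in Sample size determination: two-sided pooled Z-test, 90% power, equal groups. With p̄ the mean of p1 and p2, the formula is

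n = [z(1−α/2)·√(2p̄(1−p̄)) + z(0.90)·√(p1(1−p1)+p2(1−p2))]² / (p2−p1)²

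- CQ, α = 0.05: p1 = 0.68, p2 = 1 − 0.4 × 0.32 = 0.872. n = [1.960 × 0.5896 + 1.2816 × 0.5738]² / 0.192² = 3.576 / 0.03686 = 97. Stated: 97. (Using the rounded 0.87 gives 100.)
- CQ, α = 0.025: 0.68 against 0.87 gives 118. Stated: 118.
- AL, α = 0.05: p1 = 0.58, p2 = 1 − 0.4 × 0.42 = 0.832 gives 67, and the rounded 0.83 gives 68. Stated: 68.

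All three figures reproduce. Each concerns PQ against no PQ within one drug, so none changes with the rule chosen for AL or CQ. Under either rule, PQ is randomised among G6PD-normal patients on the same drug.

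**Step 5. Illustrate the cost of reading AL versus CQ as randomised.** The protocol gives no between-site figure, so this rests on assumptions: the drugs are truly equal, recurrence is 32% at one site and higher by s at the other, there are 120 patients per arm, and the test is a two-sided pooled Z-test at 0.05. For s = 0.10:

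- p̄ = 0.37; null SE = √(2 × 0.37 × 0.63 / 120) = 0.0623
- alternative SE = √((0.32 × 0.68 + 0.42 × 0.58) / 120) = 0.0620
- P(significant) ≈ 1 − Φ((1.96 × 0.0623 − 0.10) / 0.0620) = 1 − Φ(0.36) ≈ 0.36

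| Assumed site difference s (points) | Chance of a nominally significant AL–CQ result |
|---|---|
| 0 | 5% |
| 5 | 13% |
| 10 | 36% |
| 15 | 66% |

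**The case against.** The strongest reply is that nothing the trial sets out to test is harmed. Every stated efficacy objective is within drug, the sample size is built on adding PQ, and PQ is randomised within site even under item 4. No section names an AL versus CQ test. The Data analysis plan asks for failure proportions with confidence intervals in each arm and side-effect frequencies by arm, which is description. Calling the trial randomised is also correct if the word refers to PQ, as the end of the Introduction suggests. On this view the defect is one loose sentence.

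Most of that stands, and it limits the point. A reader might infer more than the documents support in three ways:

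- **That the main results are confounded with site.** They are not, for the reasons above.
- **That the haemoglobin comparison is compromised.** It is defined as PQ against no PQ, and both groups exist at each site.
- **That the earlier study's day-42 success rates of 68% (CQ) and 58% (AL) indicate a 10-point site effect.** Those rates are results by drug in a previous study and say nothing about differences between these sites.

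What the reply does not remove is the contradiction itself. Two sections give instructions that cannot both be carried out, and a statistical analysis plan cannot settle how patients are allocated. The wording on arms in Study Design and Safety end points is also wide enough to admit an AL–CQ comparison.

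**Conclusion.** The contradiction is real and needs correcting before enrolment. The schedule favours site-based allocation, but the protocol does not settle the matter. If allocation is by site, aliasing of drug with site is complete: any AL versus CQ or AL+PQ versus CQ+PQ difference is non-randomised, and a difference in the PQ effect between partner drugs could equally be a difference between sites. If AL or CQ is truly randomised within each site, this problem disappears.

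The scope is limited to cross-drug comparisons and the description of the design. The within-drug primary contrasts and the figures 97, 118 and 68 are unaffected. The size of any site effect is unknown; the 13% to 66% range for site differences of 5 to 15 points is an illustration under the stated assumptions, not an estimate for these sites.

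**What to change.** Make Study Design, Intervention or treatment, Laboratory Evaluations item 4 and Annex VI state one rule.

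**If allocation is by site:**

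- Delete the sentence that randomises patients to AL or CQ, and state that only PQ is randomised, within site.
- Limit the comparisons in Study Design and Safety end points to PQ contrasts within drug, with any AL versus CQ figures labelled descriptive and non-randomised.
- Stratify any analysis that pools PQ against no PQ across drugs (haemoglobin, adverse events, recurrences) by site, which is the same as by drug. This keeps each pooled comparison within site; its detail can sit in the analysis plan.

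This costs wording only. No sample size changes.

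**If AL or CQ is to be randomised:**

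- Correct item 4, add a randomisation step before the first dose to the Annex VI day 0 schedule, and randomise within each site.

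This costs stocking both drugs at both sites and preparing one randomisation list per site. No stated objective or sample size covers an AL versus CQ contrast, so choosing this option would not by itself make that contrast a powered comparison.
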